## 16.2 Additional Analyses

### 16.2.1 Cost Effectiveness Analyses

The cost effectiveness analyses to be done are twofold: One analysis will compare the cost-effectiveness different frequencies of screening – i.e. six months versus every twelve; and yearly versus having a stopping rule. The second analysis will compare the cost-effectiveness analysis of the intervention when treatment is triggered based on an 80% to 89% coverage versus triggering it based on a 90% coverage.

For both types of analysis, the measure of effectiveness will be the *proportion of communities fulfilling the “stopping” criteria after the 3 years*. And, for both types of analysis, we will use the approach the incremental cost effectiveness analysis ratio (ICER) approach by which the ICER is calculated as:

$$ICER_{AversusB} = \frac{C_A - C_B}{E_A - E_B}$$

where  $C_i$  for  $i=A, B$  is the cost of following strategy  $i$  (accumulated costs of strategy  $i$ , which are discounted at the 5% discount rate when aggregated in a multiyear period); and  $E_i$  is the value of that the measure of effectiveness takes following strategy  $i$ .

#### 16.2.1.1 FREQUENCY: 1. SIX MONTHLY VERSUS YEARLY; 2. YEARLY VERSUS STOPPING RULE

To compare the Trachoma control intervention with a 6 months frequency to that of 12 months frequency (in Niger) we will first of all calculate the average cost per community (adding those recurrent costs to those prorated capital costs and the laboratory costs) in the 6 months arm. We will do the same for those communities in the 12 months arm. Then, we will apply an

incremental cost effectiveness analysis approach and we will calculate the ratio resulting from dividing the differences in average cost of those two modalities of intervention by the difference in their average effectiveness.

To compare the yearly screening versus the stopping rule interventions in Tanzania and The Gambia, we will do similarly and calculate the average cost and average effectiveness of those communities in each arm. Then, we will calculate the incremental cost effectiveness ratio by dividing the cost differential by the effectiveness differential.

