#### **4.3.1 Details on Randomization for Niger**

Figure 1 illustrates the sampling plan for Niger. We will be working in the Matameye department of the Zinder Region. We will randomize at the grappe level.

For randomization, we stratified based on geography and endemicity. As indicated above, we began with six CSIs. Each of these six CSIs contributed 8 grappes to the study—with two grappes per CSI allocated to each of the 4 arms (for a total of twelve grappes in each of four arms, or 48 total). Moreover, we ranked the eight grappes from each CSI by clinical activity in 0-5 year old children. The top four of these were considered higher prevalence, and the lower four were considered lower prevalence. When randomizing, one higher prevalence grappe from each CSI was randomized to each treatment arm, and one lower prevalence grappe was randomized to each treatment arm. Finally, each study arm has one randomly chosen grappe intended for detailed longitudinal follow-up.

Each of the 48 grappes will have a complete census; the census will be used to randomly select children as well as provide the basis for data on treatment according to randomization into treatment arm. After the census, we will have a complete listing of all children five years or younger. One hundred of these children will be randomly selected, by assigning each child a random number and choosing the children 0-5 years associated with the lowest 100 numbers (or all children if a grappe has less than 100 in this age group). A second group of 20 children will be randomly selected as a substitution group if not all children from the first group of 100 are available. If a child on the list of 100 is not examined, the reason will be recorded (anticipated reasons include: moved to nearby grappe, moved to Maradi, Zinder, or Nigeria, absent for the day, absent more than 1 month, sick, or guardian refused). In addition, 40 adults (age 15+) will be randomly selected for monitoring at each collection.

[figure not shown]

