## Chapter 5: Eligibility, Consent and Enrollment

### 5.1 Eligible Communities

This study aims to determine the impact of different approaches to mass treatment on prevalence of trachoma and infection in villages that are hyperendemic, mesoendemic, and hypo-endemic for trachoma. Within each country, there may be communities that may fall into each category, but in general the hyperendemic communities will be located in Niger, the mesoendemic communities in Tanzania, and the hypo-endemic villages in The Gambia, based on previous surveys. Eligible communities for each country are described below:

To be eligible for the trial in Niger, a community must meet the following criteria:

1. The community must be located in the target district around Matameye
2. The village chief consents to participation in the trial (this does not obviate the need for individual consent, but without overall leadership consent, the community as a whole cannot be part of the trial)
3. The prevalence of TF/TI in the community must be  $>10.5\%$ .
4. Communities must be more than four kilometers away from the center of any semi-urban areas, which are thought to have a lower prevalence of trachoma
5. Communities must have an estimated population of between 250-600 people.

To be eligible for the trial in Tanzania, a community must meet the following criteria:

1. The community must be located in the Kongwa District
2. The community leadership gives consent that the mtaa is willing to participate in the trial (this does not obviate the need for individual consent, but without overall leadership consent, the community as a whole cannot be part of the trial)
3. The estimate of the village prevalence of trachoma is 20% or greater in preschool age children. For Tanzania, we want to concentrate on trachoma endemicity that is not at the level of virtual elimination, as we will have ample numbers of communities from The Gambia that fall into this range.
4. If the population estimate from the last Tanzania census for the community is greater than 5,000 persons, the village is not included. This will effectively exclude Kongwa town and two large communities on the main road. We excluded them because the need to do census updates and mass treatment in these communities will consume excessive time for our team. If the population estimate for an mtaa is less than 1,000 persons, and it geographically cannot be combined with another mtaa, it is excluded.

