### 6.1 Overview

In this Chapter, we discuss the procedures for conducting census of communities. The census is a critical piece of data collection, as it is the document by which we measure coverage of mass treatment in the community, and it is the sampling frame for drawing a random sample of children in each community. Once the communities have been selected, and agree to participate as described in Chapter 5 for each country, the survey teams will then conduct a full census. The methods for conducting the census will be the same for all countries.

In the context of this trial, as described earlier, the community in Tanzania is an mtaa or cluster of mtaas (population between 1,000 and 2,000 persons); in the Gambia, it is Enumeration areas (population between 600- 800 persons); and in Niger, the community is a grappe (population between 250 – 600 persons).

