### 9.1 Overview

The cost effectiveness analysis will be based on community cost estimates that we will calculate using the cost collection instruments described below. For each community, we will collect cost information regarding: all medical and non-medical personnel involved in the study and all consumables used. We will also include laboratory costs attributable to screening/treating each community. The totality of the equipment costs - such as vehicles and field equipment costs – and laboratory costs will be recorded aggregately and then allocated to each community according to the community population.

The cost collection *per se* will be organized as follows:

For each field trip/intervention, a designated member of the team will fill out the recurrent costs forms. Equally, this designated member of the team will be in charge of filling out the capital costs that are only incurred once for resources shared across different communities.

The filled forms will be double entered using the data entry software “Access” by two different data entry clerks. The double-entered data will be verified, and any differences in data entry will be checked against the paper forms. The verified dataset will be sent to our health economist [name] who will analyze the data.

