#### 16.2.1.2 COVERAGE: 80%-89% COVERAGE VERSUS 90%+ COVERAGE

Equally, to compare the 80%-89% versus the 90%+ interventions, we will do similarly and calculate the average cost and average effectiveness of those communities in each arm. Then, we will calculate the incremental cost effectiveness ratio by dividing the cost differential by the effectiveness differential.

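### The cost-effectiveness ratios use unadjusted mean cost per community, so chance differences in community size add avoidable noise to the cost comparison, mainly in Niger and Tanzania

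*Protocol*

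**What the plan says.** Section 16.2.1.1 fixes the cost measure for the Niger frequency comparison: "we will first of all calculate the average cost per community (adding those recurrent costs to those prorated capital costs and the laboratory costs". The ICER is then obtained by "dividing the differences in average cost of those two modalities of intervention by the difference in their average effectiveness". For yearly treatment against the stopping rule in Tanzania and The Gambia, "we will do similarly and calculate the average cost and average effectiveness of those communities in each arm". Section 16.2.1.2 applies the same method to coverage: "calculate the average cost and average effectiveness of those communities in each arm". Effectiveness is the proportion of communities that meet the stopping criteria after three years (16.2.1).

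Section 9.1 ties part of the cost to population: equipment and "laboratory costs will be recorded aggregately and then allocated to each community according to the community population". Sections 9.2 and 10.8 (Form 0) treat capital costs in the same way.

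On community size:
- Niger (5.1): "Communities must have an estimated population of between 250-600 people".
- Tanzania (6.1): "population between 1,000 and 2,000 persons".
- The Gambia (6.1): enumeration areas of 600 to 800 people.

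On allocation:
- Niger (4.3.1): "For randomization, we stratified based on geography and endemicity".
- Tanzania (4.3.2): constrained randomisation that balances on baseline trachoma.
- The Gambia (4.3.3): one district assigned to each cell by random number.

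Population is not named as a balancing factor in any country.

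**The concern.** A community with twice as many residents needs about twice the doses and, under the rule in section 9.1, carries twice the prorated equipment and laboratory cost. For the prorated components, the ratio of arm means is simply the ratio of mean populations, because the rule as worded contains no information about arm or number of rounds. The effectiveness measure counts each community once, whatever its size. If one arm happens to draw larger communities, it looks dearer for that reason alone, and the plan has no step that removes the effect.

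Section 1.1 names cost-effectiveness as one of the trial's two major activities, and section 1.2 asks whether six-monthly treatment of children is more cost-effective than yearly treatment of everyone. A cost difference of several per cent that reflects only size would blur that answer.

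**Working it through.** The protocol states no cost, ICER or cost precision, so there is no figure of its own to reproduce. The check asks how far mean community size can differ between two randomised groups by chance, and how much of that reaches the cost difference.

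**Inputs from the protocol**
- Size range: Niger 250–600 (5.1), Tanzania 1,000–2,000 (4.4.1, 6.1), The Gambia 600–800 (6.1).
- Ratio of largest to smallest: 600/250 = 2.40; 2,000/1,000 = 2.00; 800/600 = 1.33.
- Communities per factor level: Niger 24 v 24 (4.3.1), Tanzania 16 v 16 (4.4.1), The Gambia 24 v 24 enumeration areas (Table 1).

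**Assumptions**
- Sizes are uniform over the stated range, so SD = range/√12.
- A share *f* of community cost is proportional to population and the rest is fixed per community. The documents do not give *f*.

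**Formula.** With CV = SD/mean and n communities per level, the standard error of the relative difference in mean size is CV × √(2/n). The 95% chance range of the cost difference is about ±1.96 × *f* × CV × √(2/n).

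**Results with f = 1**
- Niger: SD = 350/√12 = 101, mean 425, CV = 0.238. SE = 0.238 × √(2/24) = 6.9%; 95% range ±13.4%.
- Tanzania: SD = 1,000/√12 = 289, mean 1,500, CV = 0.192. SE = 0.192 × √(2/16) = 6.8%; 95% range ±13.3%.
- The Gambia: SD = 200/√12 = 58, mean 700, CV = 0.082. SE = 0.082 × √(2/24) = 2.4%; 95% range ±4.7%.

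**Sensitivity to the size distribution.** Sections 3 and 4.3 give averages of 375 (Niger) and around 1,200 (Tanzania), below the midpoints used above. With those means, 700 for The Gambia, and SD from range/6 to range/4, the 95% ranges at *f* = 1 are:
- Niger: ±8.8% to 13.2%
- Tanzania: ±9.6% to 14.4%
- The Gambia: ±2.7% to 4.0%

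**Sensitivity to the share of cost that scales.** A simulation of 20,000 replicates with uniform sizes gave, for Niger:

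| Share *f* | 95% range of cost difference | P(above 5% either way) | P(above 10% either way) |
|---|---|---|---|
| 1 | −12.5% to +14.5% | 47% | 14% |
| 0.75 | −9.6% to +10.7% | 33% | 5% |
| 0.5 | −6.6% to +6.9% | 14% | 0.4% |
| 0.25 | −3.3% to +3.5% | 0.4% | 0% |

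Tanzania is almost the same: −6.3% to +6.8% at one half and −3.3% to +3.4% at one quarter.

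The Gambian figure treats enumeration areas as individually randomised. In fact one district is assigned to each cell, and district populations run from 14,964 to 18,866 (ratio 1.26), so it is only a guide there.

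**The case against.** Four points on the other side carry weight.

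- **The unadjusted difference is valid.** Under randomisation it is unbiased, and cost per community matches the unit of the effectiveness measure. A reader might infer that the plan biases the ICER towards one strategy. In Niger and Tanzania the documents do not support that; the effect is extra variance. This also means that the per-community unit can stay.
- **Not all cost scales with size.** Surveys are capped at about 100 children per community, with one examination day and one catch-up day (4.3, 7.1). Treatment in Niger and The Gambia is organised in a limited number of days or visits (8.2, 8.4), and staff and travel are costed per field day (10.8). So ±13% is an upper figure under uniform sizes, and the lower rows of the table are plausible.
- **The ICER denominator is noisier still.** If the proportions of communities meeting the criteria lie between 0.5 and 0.8 (an assumption), the 95% range of their difference is about ±28 to 35 percentage points for 16 v 16 and ±23 to 28 for 24 v 24. Tightening the numerator will not by itself make the ratio precise.
- **Size will be visible.** Section 16.1 plans to compare average community size between arms. It allows baseline differences to enter models as explanatory variables, but in the context of the prevalence analysis; it does not extend this to the ICER.

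One could also argue that covariate adjustment belongs in a later analysis plan. However, sections 16.2.1.1 and 16.2.1.2 do specify the estimator, so it is fair to improve it there.

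Two further inferences go too far. Size does not vary more than two-fold everywhere: that is true of Niger only, with Tanzania at 2.0 and The Gambia at 1.33. Nor can the noise be said to match the smaller saving expected from the stopping rule. Section 4.4.1 expects 40% to 80% of communities to stop after one or two rounds, which is 0.4 × 1/3 = 13% to 0.8 × 2/3 = 53% of rounds. That is a share of treatment rounds, whereas the noise is a share of total cost, and the two are not comparable.

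**Conclusion.** The point stands as a minor one. The protocol fixes each ICER numerator as a difference in unadjusted mean cost per community, while size varies widely in Niger and Tanzania, is not balanced by design, and enters cost through drug volume and population-based proration. The result is avoidable noise of about ±13% in Niger and Tanzania if all cost scales with population, ±7% if half does and ±3% if a quarter does. In The Gambia it is at most about ±3% to 5%. These figures rest on the assumed size distribution and on a scaling share that the documents do not give. The gain is in precision and matters mainly for Niger and Tanzania. Although section 1.1 calls cost-effectiveness a major activity, sections 1.3 and 15.4 class it as ancillary and section 16.2 lists it among additional analyses.

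**What to change.** In section 16.2.1, replace the simple difference in means by an adjusted one. Suggested text:

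*Within each country, total cost per community will be regressed on treatment arm and census population, with an intercept. The arm difference, reported at the country's mean community size, will be the numerator of the ICER. The unadjusted difference in mean cost per community will be reported alongside.*

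The baseline census count is the natural covariate, because it is fixed before treatment. The intercept allows for costs that do not depend on size, and the result remains a cost per community, so it still matches the effectiveness measure.

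The cost is one extra regression per country on data already collected. The downside is the assumption that cost is roughly linear in population; a plot of cost against population by arm would show whether that is reasonable.

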#### 16.2.1.2 COVERAGE: 80%-89% COVERAGE VERSUS 90%+ COVERAGE

Equally, to compare the 80%-89% versus the 90%+ interventions, we will do similarly and calculate the average cost and average effectiveness of those communities in each arm. Then, we will calculate the incremental cost effectiveness ratio by dividing the cost differential by the effectiveness differential.

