### 4.2 Randomization Arms

The basic structure of the trial is shown in Table 1. In this 2 X 2 factorial design, communities in each location will be randomized into four treatment arms, but these arms will differ by country. All communities will receive mass treatment with azithromycin at baseline. At present, recommended coverage of the community is 80% or better. We propose to evaluate the effect of two coverage targets, (estimated in children age 0 to 9 years old). The two arms would have 1:1 randomization at community level to one of two coverage targets: 80% to 89% coverage (reasonable program targets) and  $\geq 90\%$  (enhanced program coverage, requiring additional time and resources). All countries will be participating in the randomization arms for coverage, in order to determine the incremental effectiveness of extra effort in coverage in reducing infection and disease.

The second component of the antibiotic trial is frequency of administration of mass treatment. We propose two frequencies of mass antibiotic administration, yearly for everyone in the community (The Gambia, Niger, and Tanzania) and every six months for children ages twelve and under (Niger). The rates of disease and infection within Tanzania and The Gambia are not

hyperendemic, and the resources to mass treat more than yearly cannot be justified. Research in Tanzania has shown that re-emergence across households takes about one year, suggesting this interval is reasonable. Therefore, for communities within Tanzania and The Gambia, we propose an alternative frequency regime: communities receiving yearly mass treatment will be further randomized to two arms: yearly mass treatment every year for three years (similar to the Nigerien arm), versus an arm that allows mass treatment cessation if the community achieves our clinical or infection goals. These goals are a prevalence rate in 0-5 year olds of less than 5% trachoma (defined as TF rates less than 5%) or 5% infection (defined as laboratory positive rate of less than 5%).

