At the end of the day of mass treatment in all grappes, health workers will tally the number of individuals recorded on the census who have been treated. For those grappes assigned to the standard coverage arm, if 80% coverage has been achieved, no additional treatment days will be necessary. If 80% coverage has not been reached, one extra day will be scheduled and health workers will inform village chiefs and community members of the date of their return. After two visits, mass treatment will conclude for that community, regardless of the attained coverage. In the case of over or under treatment for that round, the community will still be analyzed on an "intent to treat" basis as described in Chapter 16, data analyses plan.

For those grappes assigned to the enhanced (>90% or more) coverage arm, up to three additional treatment days (for a total of four days) can be scheduled. Before returning for each follow-up day, health workers will compile a list of all individuals recorded on the census who did not yet receive mass treatment. Village leaders and trachoma volunteers will be given this updated list and asked to identify and mobilize those who missed treatment, informing them of the date of the return visit and encouraging their participation in follow-up visits. After four visits, mass treatment will conclude for that community, regardless of the attained coverage.

All those who present for treatment will be treated. This is true even in communities randomized to standard treatment, meaning that coverage could be as high or higher in communities randomized to standard treatment as those assigned to enhanced coverage.

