### 17.2 PRET Executive Committee

The PRET Executive Committee comprised of [name], [name] and [name] and the Chair, [name] is responsible for oversight of the partnership. The committee will be charged with the following:

- Overall project review; review of progress at yearly meetings, review of data coordination and management at 6 monthly conference calls
- Receiving recommendations from the DSMC and implementation of recommendations
- Making recommendations for resource allocation. Johns Hopkins University will serve as the primary accounting body for the partnership.
- Review of quality assurance reports from the CC of each center, and the reports on laboratory and trachoma quality assurance, and make recommendations to the study site principal investigators.
- Serve as a writing committee to oversee the draft of manuscripts using data from more than one site

We have created specific objectives to meet the overall goal of this project, and activities and milestones that chart the successful completion of each objective. The committee will use these milestones to monitor the ongoing progress of our project, and report every six months to all partners. The main evaluation component of the antibiotic intervention part of PRET will be the following: The determination of a cost effective treatment coverage and frequency to achieve rapid elimination of ocular *C. trachomatis* infection and disease reduction, and the development of guidelines for “graduating” communities to maximize program resources.

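### The planned cost-effectiveness ratios for coverage and for frequency each average over the other factor, although the extra cost of higher coverage depends on the number of treatment rounds

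*Protocol*

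**What the plan says.** Section 16.2.1 opens its plan with "The cost effectiveness analyses to be done are twofold": one comparison is of frequency (six-monthly versus yearly, or yearly versus stopping rule) and the other of coverage (80-89% versus 90% or more). Both use an ICER. The cost term "is the cost of following strategy" i, "discounted at the 5% discount rate when aggregated in a multiyear period". The effect is the proportion of communities that meet the stopping criteria after three years.

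- **Frequency (Section 16.2.1.1).** For Niger, "we will first of all calculate the average cost per community" in the six-month arm, then the same in the 12-month arm. Yearly versus stopping rule is handled alike in Tanzania and The Gambia. Coverage is not held fixed.
- **Coverage (Section 16.2.1.2).** The plan is to "calculate the average cost and average effectiveness of those communities in each arm" and divide the differences. Frequency is not held fixed.
- **Design (Section 4.2).** "communities in each location will be randomized into four treatment arms, but these arms will differ by country". Table 1 gives equal cells: 12 communities each in Niger and The Gambia, 8 in Tanzania.
- **Decision (Section 17.2).** The main evaluation component is "The determination of a cost effective treatment coverage and frequency to achieve rapid elimination".
- **Interaction.** Section 16.1.1 says the interventions may interact and puts an interaction term in the community-level efficacy model. The cost analysis has no counterpart.

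**The concern.** Because the cells are equal, comparing the two levels of one factor without stratification mixes the two levels of the other factor 50:50. That is harmless if costs and effects are additive. The cost side is not additive on its face: the additional visits for enhanced coverage recur at each round, and the number of rounds is what the frequency factor changes. A programme chooses coverage and frequency together. An averaged ratio could make extra coverage look dearer than it is under one frequency and cheaper than it is under the other, and it cannot show whether one of the four combinations is dominated.

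**Working it through.** The protocol states no cost, effect or ratio, so there is no figure to reproduce. The check counts the extra field days that the visit rules imply for enhanced coverage.

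**Inputs**
- Rounds over three years (Table 1): Niger 3 annual or 6 biannual; The Gambia 3 yearly, or at most 3 under the stopping rule.
- Niger visits per round (Section 8.2): standard coverage ends after at most 2 visits; enhanced coverage has "up to three additional treatment days (for a total of four days) can be scheduled". Difference between the maxima: 4 - 2 = 2 days per round.
- The Gambia (Section 8.4): one extra day per round for enhanced coverage.
- Tanzania (Section 8.3): extra days depend on the running tally, so no fixed count is possible.
- Stopping (Section 4.4.1): 40% to 80% of stopping-rule communities are expected to stop after one or two rounds.

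**Niger, extra days = days per round x rounds**
- Annual: 2 x 3 = 6. Biannual: 2 x 6 = 12. Averaged: (6 + 12)/2 = 9.
- 9/6 = 1.50 and 9/12 = 0.75.
- Discounted at 5%, with rounds at the times in Table 3 of Section 7.6: 5.7, 11.3 and 8.5, so 49% above and 25% below.
- The relative gaps do not depend on 2 days per round. With 3 extra days they are 9, 18 and 13.5, which gives the same ratios.

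**Sensitivity to the cost of a child-only day.** Biannual rounds treat only children aged 12 and under, so an extra day may cost less. Let it cost k times an extra day in an all-age round; k is an assumption. Undiscounted, averaged/annual = 0.5 + k and averaged/biannual = 0.5 + 0.25/k:

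| k | averaged v annual | averaged v biannual |
|---|---|---|
| 1 | +50% | -25% |
| 0.75 | +25% | -17% |
| 0.5 | 0% | 0% |

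If the effect of coverage is equal in both cells, the ICERs differ by these same factors. If it is not, they can differ even at k = 0.5. As an illustration with assumed effects of 0.40 (annual) and 0.10 (biannual), in discounted field-day units:
- k = 1: 5.7/0.40 = 14.3; 11.3/0.10 = 113.0; averaged 17.0/0.50 = 34.0.
- k = 0.5: 14.3; 5.65/0.10 = 56.5; averaged 11.4/0.50 = 22.7.

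**The Gambia**
- Yearly: 1 x 3 = 3 days.
- Stopping rule: 80% stopping after round one gives 0.8 x 1 + 0.2 x 3 = 1.4; 40% stopping after round two gives 0.4 x 2 + 0.6 x 3 = 2.6.
- Averaged: (3 + 1.4)/2 = 2.2 to (3 + 2.6)/2 = 2.8, which is 27% to 7% below the yearly value.

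This count assumes that coverage does not change when communities stop. It may: higher coverage could bring a community to the stopping criteria sooner and save whole rounds.

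**The case against.** The main objections to pressing this further are these.

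- **Marginal contrasts suit a factorial trial.** They match the separately posed research questions in Section 1.2 and use every community. With near-additive costs and effects they are usable. A reader might infer that the averaged ratios describe no strategy a programme could choose; that goes too far, since an average over the other factor can still be informative.
- **Interaction is not projected.** A reader might take Section 4.4.1 to forecast it. That section gives 10% versus 1% for annual versus biannual, and 2% versus 13% for coverage under three annual treatments. It gives no coverage effect within the biannual arms. The projections cannot simply be combined, since (2 + 13)/2 = 7.5%, not 10%. The power calculation assumes no interaction, and Section 16.1.1 says only that there may be one.
- **A large discrepancy in cost per point is not supported.** Writing e for the extra cost per round, one might set 3e/11 = 0.27e per prevalence point (annual) against 6e/2 = 3e (biannual), about 11-fold. The plan's effect is the proportion of communities meeting the stopping criteria, not prevalence points, and the 2-point gain is an inference that the protocol does not state.
- **Joint optimisation is planned.** Section 16.2.2 will seek the most cost-effective coverage, frequency and duration. This is a real mitigation, but it comes from a transmission model. It does not change what the trial-based ratios estimate.
- **The analysis is ancillary and nothing is lost.** Costs are recorded by community (Section 9.1), so cell results can be produced at any time.

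These points limit the size and urgency. They do not remove the mismatch between two averaged ratios and a joint decision.

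**Conclusion.** The concern holds in a limited form. Sections 16.2.1 to 16.2.1.2 commit to two ratios, each averaged over the other factor, while the decision in Section 17.2 is joint. The cost of enhanced coverage depends on the number of rounds, so the averaged ratio can misstate the value of coverage within a given frequency strategy. In Niger the cost increment is off by between nothing (a child-only extra day costing half as much) and 50% above the annual and 25% below the biannual value (equal day cost). With equal effects the ratio is off by the same amount. In The Gambia the averaged increment is 7% to 27% below the yearly value, given the protocol's 40-80% stopping range and equal stopping in both coverage arms. How far the ratios themselves diverge depends on effects that the protocol does not give. This is an inexpensive improvement to an ancillary analysis, not a flaw in the trial's primary comparisons.

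**What to change.** In Section 16.2.1 add that, in each country, mean cost and mean effect (proportion of communities meeting the stopping criteria) will be reported for the four randomised cells. Order the four strategies by cost and give incremental ratios between them with uncertainty intervals. Flag apparent dominance, but do not discard a strategy on point estimates. Keep the two planned ICERs beside these, and state that each is an average over the other factor.

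The cost is analysis wording only, since cost data are already gathered by community. The downside is precision. The effect is yes/no per community, so the standard error of a difference between two cells is at most sqrt(2 x 0.25/n): 0.25 with 8 communities and 0.20 with 12. For the marginal contrasts it is 0.18 (16 per level) and 0.14 (24 per level). In The Gambia each cell is a single district (Section 4.3.3), so these figures leave out any district-level variation. Ratios with a small effect difference in the denominator will be unstable, so the cell means should be shown as well as the ratios.
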